## PARTICIPANT AND HOUSEHOLD ELIGIBILITY

Participants will be on primarily recruited amongst rural agricultural workers that often work and sleep overnight away from the village during the wet season. Households must enrol at least five eligible participants to enter the trial. Participants must be aged 6-60 years to take part in the trial.

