## STATISTICAL CONSIDERATIONS

### Sample Size Calculation

An initial target of 1,000 households was based on the power calculation below (Table 3). The only reliable clinical data from the study area at the time was 32% prevalence of *P. falciparum* from village surveys during September. The incidence over 9 months sampling was estimated to be 2-6%. Hill *et al.* [23] found 80% reduction in cases in their repellent group and Rowland *et al.* (2004b) found a 44% reduction in *P. falciparum*; therefore a 30-50% reduction was used in the calculations.

Sample sizes were recalculated following the first year’s data collection which found a 0.7% incidence of malaria. A sample size of 633 households per arm would therefore be necessary to detect a 50% intervention effect with 95% significance and 80% power. Non-compliance in the first year was around 27%, so the sample size was adjusted to 804 households per arm.

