### Table 4. Revised sample size calculation following first year of data collection (giving a firmer estimate of malaria incidence), calculations are for different scenarios of effect with 95% significance and 80% power

| Assumed Incidence | Intervention Effect | Coefficient of variation (K) | Households Per Arm | Increase 27%  (Loss From Non-Compliance) |
| --- | --- | --- | --- | --- |
| 0.010 | 50% | 0.25 | 948 | 1204 |
| 0.015 | 50% | 0.25 | 633 | 804 |
| 0.020 | 50% | 0.25 | 476 | 605 |
| 0.010 | 40% | 0.25 | 1579 | 2006 |
| 0.015 | 40% | 0.25 | 1054 | 1336 |
| 0.020 | 40% | 0.25 | 792 | 1006 |
| 0.010 | 30% | 0.25 | 2982 | 3787 |
| 0.015 | 30% | 0.25 | 1991 | 2529 |
| 0.020 | 30% | 0.25 | 1495 | 1899 |

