## DATA HANDLING AND RECORD KEEPING

### Data Analyses and Handling

Only the consent forms will contain personal information (names) and these will be stored for the length of the trial in a locked filing cabinet in the project office in Vientiane. Number codes will be used to identify participants during baseline and monthly surveys. Data will be entered into a password protected Microsoft Access database.

The initial analysis will be performed according to intention-to-treat. This will include all participants who were recruited to the trial and gave every monthly RDT result. An additional per protocol analysis will be carried out. This will include only those participants who slept under a bed net and used the lotion in the evenings at least 90% of the time. Positive cases will be subsequently excluded from the trial due to the possibility of them testing positive in later months from the same episode.

Data from both arms from baseline surveys will be compared by ANOVA. Comparison of *P. falciparum*, *P. vivax* and fever incidence between the trial arms will be carried out by poisson regression adjusted for intracluster (household) variation by random effects methods. Comparison of seroconversion for dengue, Japanese Encephalitis and scrub typhus between trial arms will be done using a chi-squared test on numbers seroconverted or not seroconverted over the course of the trial.
An assessment of compliance will be carried out looking in particular at repellent and placebo use and LLIN use. Adverse events in children under 12 years and in participants over 12 years will also be assessed.

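### The 27% non-compliance allowance is computed as n × 1.27 rather than n ÷ 0.73, and an allowance for loss does not fit the intention-to-treat analysis, so 80% power at 804 households per arm is not assured

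*Protocol*

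**What the plan says.** The protocol, under Sample Size Calculation, gives the revised requirement after the first year: "A sample size of 633 households per arm would therefore be necessary", a number said to be "necessary to detect a 50% intervention effect with 95% significance and 80% power". It then adjusts: "Non-compliance in the first year was around 27%, so the sample size was adjusted to 804 households per arm". The matching row of Table 4 (incidence, effect, K, households, adjusted households) reads "0.015 | 50% | 0.25 | 633 | 804", and the heading of the last column describes the 27% increase as "Loss From Non-Compliance".

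Under Data Analyses and Handling, "The initial analysis will be performed according to intention-to-treat". That set is defined by recruitment and a complete series of monthly RDT results. Use of the net and lotion, with a 90% threshold, decides membership of the additional per-protocol set only. The same section describes the assessment of compliance in terms of lotion and LLIN use. The protocol does not say what the first-year 27% measured.

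**The concern.** There are two problems with one number.

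- **Arithmetic.** To have n households left after losing a fraction d, one enrols n/(1 − d). Multiplying by 1 + d always falls short, and the shortfall is material at d = 0.27.
- **Fit to the analysis.** An inflation for loss is right only for people who leave the analysis set. Under the protocol's own definition, a person who does not use the lotion but gives every RDT result stays in the intention-to-treat set. That person does not reduce the number analysed. They pull the arms together, and a loss factor is not designed to cover that.

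At stake is how a null result would be read. The protocol presents 804 per arm as the size that secures 80% power for a 50% effect after allowing for non-compliance. If that power is not there, an inconclusive intention-to-treat result could be mistaken for good evidence against an effect of that size.

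**Working it through.** **Inputs.** From Table 4 and the sample size text: control incidence r0 = 0.015, effect 50% (r1 = 0.0075), K = 0.25, 80% power, 95% significance (taken as two-sided 5%), and non-compliance d = 0.27. Household size m = 5: eligibility says "Households must enrol at least five eligible participants to enter the trial", and 8,000 subjects in 300 + 1,300 = 1,600 households also gives 5.

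**1. Reproduce 633.** The protocol names no formula. The standard unmatched cluster formula for rates is

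c = 1 + (1.96 + 0.842)² × V / (r0 − r1)², with V = (r0 + r1)/m + K²(r0² + r1²).

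Here V = 0.0225/5 + 0.0625 × 0.00028125 = 0.0045176 and (r0 − r1)² = 0.00005625, so V/(r0 − r1)² = 80.31 and c = 631.4, against 633 stated. The same formula reproduces every row of Tables 3 and 4 within 1%. A binomial variance gives 623.5 and changes the powers at 804 below by less than one percentage point.

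**2. Reproduce 804.** 633 × 1.27 = 803.9. Eight of the nine adjusted entries in Table 4 equal n × 1.27 to within one household; the ninth is 1,336 against 1,338.6. None equals n/0.73.

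**3. If the 27% are lost from analysis.**

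- Remaining: 804 × 0.73 = 586.9, about 587, below 633.
- Power = Φ(√[(586.9 − 1)/80.31] − 1.96) = Φ(2.701 − 1.960) = 77.1%. Removing individuals rather than households (m = 5 × 0.73 = 3.65) also gives 77.1%.
- Correct inflation: 633/0.73 = 867.1, so 868. Power with 868 enrolled and 27% lost is 80.1%.
- Whole column, n/0.73 rounded up, in Table 4 order: 1,299; 868; 653; 2,164; 1,444; 1,085; 4,085; 2,728; 2,048.

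**4. If the 27% stay in the intention-to-treat set.** Assume 50% is the effect in compliers and non-compliers keep a share s of it. The overall effect is 0.5 × (0.73 + 0.27s). For s = 0 it is 36.5%, so r1 = 0.009525, V = 0.0049247, (r0 − r1)² = 0.00002998 and V/(r0 − r1)² = 164.3. Power at 804 is Φ(√[803/164.3] − 1.96) = Φ(0.251) = 59.9%. Repeating this:

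| Share of benefit kept | Overall effect | Power at 804 per arm | Per arm for 80% |
| --- | --- | --- | --- |
| none | 36.5% | 59.9% | 1,291 |
| a quarter | 39.9% | 68.5% | 1,060 |
| half | 43.3% | 76.3% | 882 |
| three quarters | 46.6% | 83.0% | 743 |
| all | 50.0% | 88.5% | 632 |

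Power reaches 80% at an overall effect of about 45%, that is, when non-compliers keep about 63% of the benefit. With the planned 1,600/2 = 800 per arm the two ends are 59.7% and 88.4%, so the difference from 804 is negligible.

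**The case against.** The strongest case on the other side accepts the wrong factor and disputes its weight.

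- **The certain error is small.** It amounts to 64 households per arm (868 − 804) and about three points of power. This stands.
- **The 27% is undefined.** The protocol's intention-to-treat set is narrower than usual because it requires every monthly RDT result. If the 27% were missed surveys or tests, those people would leave that set, the dilution point would fall, and 868 would be the whole answer. This stands as a possibility. The protocol's own description of compliance as lotion and net use makes non-use the more natural reading, but that is an inference.
- **The 50% may already be an effect in everyone randomised.** Then 804 gives 88.5% and no allowance is needed. A reader might infer the opposite from the Bolivian trial, whose 80% reduction came from a per-protocol analysis. The documents do not support that step. The sample size text pairs it with a 44% reduction from the household trial in Pakistan, described without any exclusion of non-users, and plans on 30–50%. On the other hand, adding a compliance allowance to a 50% effect suggests that the effect had not been discounted already. The point remains open.
- **No benefit at all in non-compliers is the extreme case.** With a 90% usage threshold, someone using lotion on 80% of evenings could count as non-compliant. This stands, and is why a range is needed.
- **Table 4 already shows 40% and 30% effects** (1,054 and 1,991 households at 1.5%), which bracket 36.5%. True, but nothing links those rows to non-compliance under intention-to-treat.

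**Conclusion.** The adjusted column is wrong as written. Read as the loss it is labelled, 804 per arm gives 77.1% power and the figure should be 868. This needs no assumption about who used the lotion, only the protocol's own inputs and a two-sided 5% test.

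The mismatch with the intention-to-treat analysis is real on the natural reading of the 27%, but conditional. It rests on the 27% meaning non-use, on 50% being the effect in compliers, and on how much benefit non-compliers keep. At 1.5% incidence, power at 804 per arm then lies between 59.9% and 88.5%. A reader might infer that 804 flatly fails to give 80% power, or that the trial's intention-to-treat power is 60%. The documents support neither: above about 63% of the benefit kept, power exceeds 80%. What they support is that 80% is not assured.

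The two corrections answer different questions and must not be multiplied together. The text's 0.7% incidence against the 1.5% row used for 633 and 804 is a separate matter. All power figures here stay at 1.5% so that they show this error alone.

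**What to change.** 1. State what the first-year 27% measured: non-use of lotion or net (and at what threshold), missed RDTs, or both.
2. Recompute the last column of Table 4 and the figure in the text with n/0.73 (633 becomes 868). Label the column as applying to loss from the analysis or to the per-protocol set. If the share excluded from the per-protocol set differs from 27%, use that share.
3. For intention-to-treat, state the power of the planned 800 or so per arm as a range over the benefit kept by non-compliers, about 60% to 88% at 1.5% incidence and a 50% effect in compliers. Say whether the 50% is meant as the effect in compliers or in everyone randomised.

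This is a table and text correction. It asks for no extra enrolment and changes no procedure. The only cost is a less favourable stated power.

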### Table 3. Initial sample size calculations

| Assumed incidence | Intervention effect | Coefficient of variation (K) | Power | Number of households in each arm |
| --- | --- | --- | --- | --- |
| 0.06 | 50% | 0.25 | 90% | 214 |
| 0.05 | 50% | 0.25 | 90% | 256 |
| 0.04 | 50% | 0.25 | 90% | 319 |
| 0.03 | 50% | 0.25 | 90% | 424 |
| 0.02 | 50% | 0.25 | 90% | 634 |
| 0.02 | 50% | 0.25 | 80% | 476 |
| 0.03 | 50% | 0.30 | 90% | 426 |
| 0.02 | 50% | 0.30 | 80% | 477 |
| 0.03 | 40% | 0.25 | 80% | 530 |
| 0.06 | 30% | 0.25 | 80% | 503 |

### Table 4. Revised sample size calculation following first year of data collection (giving a firmer estimate of malaria incidence), calculations are for different scenarios of effect with 95% significance and 80% power

| Assumed Incidence | Intervention Effect | Coefficient of variation (K) | Households Per Arm | Increase 27%  (Loss From Non-Compliance) |
| --- | --- | --- | --- | --- |
| 0.010 | 50% | 0.25 | 948 | 1204 |
| 0.015 | 50% | 0.25 | 633 | 804 |
| 0.020 | 50% | 0.25 | 476 | 605 |
| 0.010 | 40% | 0.25 | 1579 | 2006 |
| 0.015 | 40% | 0.25 | 1054 | 1336 |
| 0.020 | 40% | 0.25 | 792 | 1006 |
| 0.010 | 30% | 0.25 | 2982 | 3787 |
| 0.015 | 30% | 0.25 | 1991 | 2529 |
| 0.020 | 30% | 0.25 | 1495 | 1899 |

## DATA HANDLING AND RECORD KEEPING

### Data Analyses and Handling

Only the consent forms will contain personal information (names) and these will be stored for the length of the trial in a locked filing cabinet in the project office in Vientiane. Number codes will be used to identify participants during baseline and monthly surveys. Data will be entered into a password protected Microsoft Access database.

The initial analysis will be performed according to intention-to-treat. This will include all participants who were recruited to the trial and gave every monthly RDT result. An additional per protocol analysis will be carried out. This will include only those participants who slept under a bed net and used the lotion in the evenings at least 90% of the time. Positive cases will be subsequently excluded from the trial due to the possibility of them testing positive in later months from the same episode.

Data from both arms from baseline surveys will be compared by ANOVA. Comparison of *P. falciparum*, *P. vivax* and fever incidence between the trial arms will be carried out by poisson regression adjusted for intracluster (household) variation by random effects methods. Comparison of seroconversion for dengue, Japanese Encephalitis and scrub typhus between trial arms will be done using a chi-squared test on numbers seroconverted or not seroconverted over the course of the trial.
An assessment of compliance will be carried out looking in particular at repellent and placebo use and LLIN use. Adverse events in children under 12 years and in participants over 12 years will also be assessed.

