### Outcomes

The primary outcome measure will be the incidence of malaria defined as a positive rapid diagnostic test (RDT) result. Secondary outcomes will be all-cause fevers self reported via monthly questionnaires and seroconversion of dengue, JE and scrub typhus measured by ELISA test on dried bloodspots taken during baseline and exit surveys.

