## STUDY PROCEDURES AND EVALUATIONS

### Study Schedule

| Activity | 2009 | 2010 |
| --- | --- | --- |
| Design of consent form and survey forms | March | - |
| Design of database | March | - |
| Recruitment and training of Trial Coordinator | April | - |
| Design and approval of bi-lingual labels for lotions | April | - |
| Study design and SOPs approved by PSI and LSHTM | April | - |
| Translation of survey forms | April and May | - |
| Import and delivery of lotions, LLINs and RDTs | April-June | March-April |
| Gain ethics approval from LSHTM and Lao Ministry of Health | May | - |
| Training of District Health Staff | May-July & December | March-May & December |
| Selection of study villages | June | March |
| Training of VHVs | June, July & December | April, May & December |
| Recruitment and Baseline Surveys | June | April |
| Monthly follow-up Surveys | July-November | May-November |
| Evening spot checks | July-November | May-November |
| Entomology survey | July | July |
| Exit Survey | December | December |

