### Follow-up Surveys

Monthly surveys will be carried out at monthly intervals after baseline and finishing in December in both years. The questionnaire will collect data on compliance, acceptability of the lotion and malaria exposure that month. An RDT will also be carried out to actively detect malaria cases. Positive results will be confirmed by PCR in London where possible and a random selection of negative RDTs will also be confirmed in this way. Positive cases are to be given prompt treatment according to local guidelines.

The access to many villages is anticipated to become very difficult during the height of the rainy season and the study aims to continue data collection by using village health volunteers (VHVs). These volunteers have already been trained in the use of RDTs and malaria treatment and will be further trained to give out replacement repellent/placebo and complete the monthly survey forms.

Access to remote communities is anticipated to be a major obstacle in data collection, particularly during the rainy season. The use of VHVs will hopefully enable data collection to continue throughout these months. The monthly survey has been designed to be as simple as possible to enable these workers who sometimes have limited education to complete the form.

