## DISCONTINUATION CRITERIA

### Participant and Household Withdrawal

Participants may withdraw their consent to take part, as well as permission for their children to take part at any point before the end of the trial. If withdrawal takes place in the first two months of the trial, then further recruitment within the same village will be considered.

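### The analysis labelled intention-to-treat is a complete-case set that requires every monthly RDT, and its wording conflicts with the removal of positive cases

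*Protocol*

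**What the plan says.** The Protocol, Data Analyses and Handling, states: "The initial analysis will be performed according to intention-to-treat". The next sentence defines the set: "This will include all participants who were recruited to the trial and gave every monthly RDT result". After a sentence on the per-protocol set, the same paragraph adds: "Positive cases will be subsequently excluded from the trial due to the possibility of them testing positive in later months from the same episode".

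Under Outcomes, "The primary outcome measure will be the incidence of malaria defined as a positive rapid diagnostic test (RDT) result". The Study Schedule lists "Monthly follow-up Surveys | July-November | May-November" for 2009 and 2010, with the exit survey in December of each year. Under Follow-up Surveys, "Monthly surveys will be carried out at monthly intervals after baseline and finishing in December in both years", with an RDT at each survey. This gives six post-baseline rounds in 2009 (July to December) and eight in 2010 (May to December).

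The same section foresees missed visits: "The access to many villages is anticipated to become very difficult during the height of the rainy season". It plans to use village health volunteers to keep data collection going. Neither section says whether the RDT series need only be complete up to the first positive, or whether a participant with a missed RDT contributes any follow-up.

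**The concern.** An intention-to-treat analysis keeps participants as randomised. Here membership depends on having attended every round, which is known only after randomisation. A set defined in this way does not have the protection that the label promises.

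The rule also sits badly with the removal of positives. Someone who tests positive in August and then leaves the trial has no later RDTs and so has not given every monthly result. The protocol does not say how such a person is classified, yet these people are the primary outcome events.

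Even if cases are kept, the rule treats the two outcomes differently. A case at round 2 needs two completed tests, while a non-case needs six or eight. Information is lost, incidence is overstated, and the comparison is exposed to any difference in attendance between arms.

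The removal is also wider than its reason. The reason concerns repeat positives from one malaria episode. Leaving the trial would also end fever reporting and the exit blood spot, on which the secondary outcomes rest, although the Exit Survey section plans a second blood spot for all participants.

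**Working it through.** **The plan's own figure.** The 633 households per arm (Table 4: incidence 0.015, 50% effect, K = 0.25, 80% power) can be reproduced with the unmatched cluster-rate formula, five participants per household (the minimum for entry) and two-sided 5% significance (assumed):

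c = 1 + (1.960 + 0.842)² × [(λ0 + λ1)/y + K²(λ0² + λ1²)] / (λ0 − λ1)²

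= 1 + 7.849 × [0.0225/5 + 0.0625 × 0.00028125] / 0.0075² = 631.4, against the stated 633.

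The adjusted figure is 633 × 1.27 = 804. The 27% is attributed to non-compliance, not to participants lost through the every-RDT rule. The sample size arithmetic is not in dispute.

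**Literal reading.** Only cases first found at the last of V rounds have every RDT. With equal monthly risk (assumed) the share kept is 1/V: 1/6 = 16.7% in 2009 and 1/8 = 12.5% in 2010. If the December survey carried no RDT, the shares would be 1/5 and 1/7. At 804 households per arm the design expects 804 × 5 × (0.015 + 0.0075) ≈ 90 cases; one sixth is about 15 and one eighth about 11.

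**Likely reading: series complete up to the first positive or the end.** Let p be the chance of giving an RDT at each round, independent across rounds (assumed), with first positives spread evenly over V rounds.

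- Non-cases kept: p^V.
- Cases kept: the mean of p^j for j = 1 to V.
- Apparent risk: r × (cases kept) / [r × (cases kept) + (1 − r) × (non-cases kept)].

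For V = 8 and r = 0.015:

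| p | Non-cases kept | Cases kept | Apparent risk |
| --- | --- | --- | --- |
| 0.95 | 0.663 | 0.799 | 1.80% |
| 0.93 | 0.560 | 0.731 | 1.95% |
| 0.90 | 0.430 | 0.641 | 2.22% |

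For example, at p = 0.95: 0.015 × 0.799 / (0.015 × 0.799 + 0.985 × 0.663) = 0.0180. With six rounds, 0.95 and 0.90 give 73.5% and 53.1% of non-cases kept.

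**Effect on the arm comparison.**

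- Equal attendance, true risks 1.5% and 0.75%, V = 8: the apparent ratio is 0.00902/0.01802 = 0.501 at p = 0.95 and 0.01112/0.02216 = 0.502 at p = 0.90. The inflation nearly cancels.
- Unequal attendance, no true effect, 93% in the repellent arm and 95% in the placebo arm: 0.0195/0.0180 = 1.08 with eight rounds, and 1.06 with six. With the arms reversed, the ratios are 0.92 and 0.95.
- The same gap with a true ratio of 0.50 and eight rounds: 0.46 or 0.54, depending on which arm attends less.

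**Information lost.** At 804 per arm the formula gives 88.5% power. Scaling y by the share of cases kept (an approximation, because power here is driven almost wholly by the number of cases) gives about 81% for 0.799 and 72% for 0.641. Scaling everyone by the non-case share is harsher and gives about 73% and 55%.

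**The case against.** The strongest reply is that the literal reading is not what the authors meant. The reason given for removing positives is that they may test positive again later from the same episode, which presupposes that the first positive has been counted. A set without its cases would also make no sense for an incidence outcome. This stands. A reader might infer that the primary analysis discards most of its events; the documents support only a conflict in wording that needs to be settled.

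A second reply is that bias between arms is not shown. This also stands. Randomisation is by household within village, so an inaccessible village should lose both arms alike. The placebo is coded, although the protocol concedes a slight difference in smell. Village health volunteers are meant to limit missed rounds. With equal attendance the ratio hardly moves. The protocol reports no attendance, overall or by arm, so the shifts above are scenarios.

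Two further inferences are tempting but unsupported. One is that replacement recruits can never qualify. The withdrawal section says only that "further recruitment within the same village will be considered", and the series could be counted from a recruit's own entry. The other is that fever and exit data on cases will certainly be lost. The removal sentence stands in the analysis section, after the per-protocol sentence, which leaves its scope in some doubt, and the Exit Survey section points the other way.

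None of this rescues the label. On every reading, a participant who misses one RDT without having tested positive is left out of the analysis called intention-to-treat. This is not a matter left to a statistical analysis plan, because the protocol itself fixes the set.

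**Conclusion.** The plan is wrong as written. The set is a complete-case set conditioned on attendance after randomisation, and that conclusion needs no numerical assumption. The every-RDT rule and the removal of positives also conflict as worded and must be reconciled.

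The sizes rest on assumptions: independent attendance, evenly spread risk and eight rounds. With 5% or 10% of tests missed per round, 34% or 57% of non-cases and about 20% or 36% of cases are dropped, and a 1.5% risk reads as 1.8% or 2.2%. The firm consequences are lost information and overstated incidence. Distortion of the treatment effect requires attendance that differs by arm or is related to risk. A gap of two percentage points per round would move a null ratio to about 1.06 to 1.08, but the protocol has no data on whether such a gap exists.

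**What to change.** Replace the definition of the set with wording such as: *The primary analysis includes all randomised participants by allocated arm. Person-time runs from lotion issue to the first positive RDT, or to the last RDT if there is none, and enters the Poisson model as an offset. Participants with no post-baseline RDT are counted and reported by arm.* Keep the every-RDT set as a sensitivity analysis under its own name.

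State that a positive RDT ends malaria person-time only. Reconcile the removal of positives with the fever outcome under Outcomes and with the blood spot under Exit Survey.

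The cost is a few sentences, and the Poisson model with household random effects stays. Two limits remain. Censoring at the last RDT still assumes non-informative dropout, so RDT completion should be reported by arm and round. If positives were really to leave the trial, keeping them for fever and the exit blood spot means continuing visits that are already scheduled, so that part is a change in conduct and not only in analysis.

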### Malaria in Lao PDR

Malaria is a major public health problem in Lao PDR: the World Health Organization estimates that malaria was responsible for 46 lost DALYs per 100,000 population in 2004 (WHO, 2009). The prevalence of malaria recorded in Lao PDR in 1998 was 55 cases per 1,000 population; but in Attapeu the prevalence was 101 per 1,000 and in Sekong it was 163 per 1,000 the highest rate in the country (UNDP, 2001).

Current policy is for the entire population at risk (estimated to be 70% of the country) to receive insecticide treated nets (WHO, 2005). In addition free diagnosis and ACT (artemisinin combined therapy) treatment has been implemented to poor populations. Artemisine resistance has been recorded in neighbouring Cambodia, although it is not yet recorded in Laos (Singhasivanon *et al.* 2003).

In general the use of DEET (*N,N-*diethyl-*M*-toluamide) repellents by rural people is often low due to cost, but other methods of personal protection such as coils or repellents made from locally available ingredients such as neem oil are still used (Frances and Wirtz, 2005).

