## STUDY OBJECTIVES

### Objectives

The primary objective is to determine whether 15% DEET repellent used in the evening can reduce malaria incidence. Secondary objectives are to determine whether the intervention has an effect on fevers and dengue, Japanese Encephalitis (JE) and scrub typhus seroconversion. The trial will also monitor lotion acceptability and any occurrence of adverse events.

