### Exit Survey

An exit survey will be carried out during the final month of data collection, which will assess the acceptability of the repellent lotion in more detail. Another blood spot will be collected from each participant.

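### The rule removing RDT-positive participants from the trial is wider than its stated reason and conflicts with the exit blood spot and the ITT definition

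*Protocol*

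**What the plan says.** The rule stands in the Protocol, Data Analyses and Handling, straight after the two analysis sets are described: "Positive cases will be subsequently excluded from the trial due to the possibility of them testing positive in later months from the same episode". No other reason is given. The Protocol sets no time window, does not limit the rule to the malaria endpoint, and does not provide for re-entry.

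Other sections that bear on it:

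- **Outcomes.** "The primary outcome measure will be the incidence of malaria defined as a positive rapid diagnostic test (RDT) result". For the rest: "Secondary outcomes will be all-cause fevers self reported via monthly questionnaires and seroconversion of dengue, JE and scrub typhus measured by ELISA test". Serology uses a baseline and an exit blood spot.
- **Exit Survey.** "Another blood spot will be collected from each participant".
- **Data Analyses and Handling, ITT set.** "This will include all participants who were recruited to the trial and gave every monthly RDT result".
- **Data Analyses and Handling, model.** The comparison of *P. falciparum*, *P. vivax* and fever incidence "will be carried out by poisson regression adjusted for intracluster (household) variation by random effects methods".
- **Follow-up Surveys.** Positive cases are treated promptly; nothing is said about leaving the trial.
- **Participant and Household Withdrawal.** Only withdrawal of consent is listed.

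**The concern.** The stated reason is about measurement: an RDT may still be positive a month later from an infection already counted. That justifies ignoring the later positive. It has no bearing on self-reported fever, on antibodies to dengue, JE or scrub typhus, or on adverse events.

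Exclusion is triggered by the primary outcome, which the lotion is meant to change. If the lotion works, more people leave the placebo arm than the DEET arm. The fever and seroconversion comparisons would then be made on groups that differ from those randomised, in a way related to treatment. These are the declared secondary objectives: "Secondary objectives are to determine whether the intervention has an effect on fevers and dengue, Japanese Encephalitis (JE) and scrub typhus seroconversion".

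The rule also collides with two other statements in the same Protocol, so staff and analysts cannot follow all three as written.

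**Working it through.** **1. The statements side by side**

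| Statement | Consequence if the exclusion is literal |
| --- | --- |
| Exit blood spot from everyone (Exit Survey) | An excluded case gives none, so has no seroconversion result |
| Monthly fever reports (Outcomes) | They stop at the first positive |
| ITT set needs a complete monthly RDT series (Data Analyses and Handling) | A case excluded before the last survey cannot meet this |
| Prompt treatment of positives, no removal mentioned (Follow-up Surveys) | Silent on exclusion |
| Withdrawal of consent only (Participant and Household Withdrawal) | A positive RDT is not listed as a reason to leave |

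**2. Reproducing the planning figure**

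Inputs:
- Placebo incidence r0 = 0.015, effect 50% (so r1 = 0.0075) and k = 0.25, from Table 4.
- 80% power and 5% significance, taken as two-sided.
- m = 5 people per household, the minimum in the eligibility section.

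The cluster-trial formula for rates (Hayes-Bennett) is

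c = 1 + (z_0.975 + z_0.80)² × [(r0 + r1)/m + k²(r0² + r1²)] / (r0 − r1)²

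- (1.960 + 0.842)² = 7.849
- (0.015 + 0.0075)/5 = 0.0045
- 0.0625 × (0.000225 + 0.00005625) = 0.0000176
- (0.0045 + 0.0000176)/0.00005625 = 80.31
- c = 1 + 7.849 × 80.31 = 631.4, against 633 in Table 4

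The plan's figure reproduces closely, so five per household is a fair size for the next step. With the 27% increase, 633 × 1.27 = 804 households, and 804 × 5 = 4,020 people per arm. This agrees with about 4,000 per arm from the 8,000 in the Protocol Summary.

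**3. People removed (4,000 per arm, 50% effect, incidence cumulative over the season)**

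| Placebo incidence | Placebo | DEET | Share of all 8,000 | Difference between arms |
| --- | --- | --- | --- | --- |
| 0.7% (found in year 1) | 28 | 14 | 42/8,000 = 0.5% | 0.35 points |
| 1.5% (Table 4 row behind 633) | 60 | 30 | 90/8,000 = 1.1% | 0.75 points |

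These counts are slightly high, because someone first positive at the last survey loses nothing. The year-1 figure is used here as the placebo rate. If it is pooled over arms, the rates are 0.7% × 2/1.5 = 0.93% and 0.47%, or 37 vs 19 people, which lies inside the range above.

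**4. Follow-up time lost**

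In 2010 there are 8 surveys after baseline (May to December). With first positives spread evenly over them, a case loses on average 3.5 of 8 surveys, a fraction of 7/16. At 1.5% the loss is 0.015 × 7/16 = 0.7% of placebo person-time and 0.0075 × 7/16 = 0.3% of DEET person-time.

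**5. Effect on serology (illustration)**

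Assume that malaria-positive people seroconvert R times as often as the others, and that the others seroconvert equally in both arms. The Protocol gives no value for R; 2 to 4 is an assumption. With everyone kept, the DEET-to-placebo ratio is [1 + (R − 1)p1]/[1 + (R − 1)p0]. At p0 = 0.015 and p1 = 0.0075:

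- R = 2: 1.0075/1.015 = 0.993
- R = 4: 1.0225/1.045 = 0.979

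After exclusion the ratio is 1.00. The shift is towards no effect and is at most about 2% on these assumptions.

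**The case against.** The best defence is that the sentence is only an analysis convention. It stands in the data-analysis section, its reason concerns RDTs, and the operational sections describe no removal: cases are treated, everyone gives an exit blood spot, and only withdrawn consent ends participation. On that reading, malaria person-time is censored at the first positive and fever and serology continue. This is tenable, and may be what was meant, but it is not what the sentence says. It supports rewording the sentence rather than leaving it.

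Two further points of the defence stand. The numbers are small at the revised planning values. And analysing the first episode only is a common choice when monthly RDTs cannot separate persistence from reinfection. Following a case for the other species would answer a different question; leaving it out is not an error.

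Stronger readings that a reader might infer, and why they fail:

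- *The primary comparison is invalid.* The exclusion applies after the positive, which implies that the first positive is counted. Taken with the ITT condition, the rule would remove most cases from the primary analysis, but that is a conflict between two sentences to be resolved. The Protocol nowhere says that cases are not to be counted.
- *The loss runs to hundreds of people.* That needs Table 3's 6% incidence applied to Table 4's 804 households, a scenario that the plan never uses. Table 3 pairs 6% and a 50% effect with 214 households: 214 × 5 = 1,070 people per arm, so about 64 vs 32.
- *A large group is lost at entry.* The Protocol Summary mentions an RDT at baseline, but Recruitment and Baseline Survey lists none. The provincial prevalences are from 1998 and the village surveys were done in September, so neither estimates positivity at entry. A baseline positive also precedes lotion use, so its removal cannot be caused by the lotion.
- *The people lost are those most exposed to all the infections studied.* This is plausible, but the Protocol does not say it.

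**Conclusion.** The point holds as a rule worded more widely than its reason, in conflict with the exit blood spot and with the ITT condition. Followed literally, it causes loss from fever and exit serology that depends on the outcome and runs about two to one between arms at the planned effect.

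Its size is modest: about 42 to 90 people in all, 0.5-1.1% of participants. This rests on about 4,000 people per arm, a 50% effect and incidence of 0.7% to 1.5% read as cumulative over the season. The Protocol does not state the time unit of the year-1 figure. If it were monthly over 8 surveys, 1 − 0.993⁸ = 5.5% of placebo and 1 − 0.9965⁸ = 2.8% of DEET participants would be removed, and the loss would no longer be negligible. The first-episode malaria comparison is not undermined by this sentence alone.

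The sentence follows the per-protocol description, and it is unclear whether it governs both analyses. That should be settled at the same time.

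**What to change.** Replace the sentence in Data Analyses and Handling with a rule on counting:

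- After a positive RDT, malaria follow-up is censored at that positive; alternatively, repeat positives of the same species are not counted.
- The participant stays in the trial and in the ITT set, and continues to contribute fever reports, adverse events and the exit blood spot.
- The ITT condition on complete RDT results is reworded so that a case is not removed for lacking tests after the first positive.

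Then reconcile Follow-up Surveys, Exit Survey, Participant and Household Withdrawal, and Data Analyses and Handling. State whether the rule applies to a positive RDT at baseline, and whether it governs the ITT analysis, the per-protocol analysis or both.

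This changes follow-up and counting only; it takes no position on the treatment of cases. The cost is the rewording and a few extra visits in households that are already being surveyed.
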